# Design and methods of the Ixekizumab Diabetes Intervention Trial (I-DIT): protocol for a phase 2, randomised, multicentre, placebo-controlled, double-blind trial of anti-interleukin 17 as a treatment option for adults with new-onset type 1 diabetes

**DOI:** 10.1136/bmjopen-2025-103486

**Published:** 2025-11-12

**Keywords:** IMMUNOLOGY, DIABETES & ENDOCRINOLOGY, Clinical Protocols

## Abstract

**Introduction:**

Type 1 diabetes is characterised by progressive loss of pancreatic beta cells. Studies have shown that interleukin (IL)−17 is likely a mediator for this destruction. Whether inhibition of IL-17 could preserve beta cell function in people with new-onset type 1 diabetes is unknown.

**Methods and analysis:**

In this phase 2, randomised, multicentre, placebo-controlled, double-blind trial conducted at 17 study sites in Sweden, 127 adults aged 18–45 years old with newly diagnosed type 1 diabetes will be enrolled. Participants will be randomised to receive either subcutaneous IL-17 inhibitor or placebo for 52 weeks, in addition to their conventional therapy. The primary endpoint will be change in residual insulin secretion measured by the area under the curve for C-peptide in response to 2-hour mixed meal tolerance test between baseline and week 52. Additionally, masked continuous glucose monitoring will be performed during 14 days at the run-in period, week 13, week 26 and week 52. Secondary endpoints will be change in time in glucose range (3.9–10 mmol/L), time in hypoglycaemia (<3.9 mmol/L), HbA1c and mean insulin dosage per kilogram body weight. Patient-reported outcomes will be evaluated with questionnaires at baseline, week 26 and 52. Additionally, 1 and 3 years after the end of the treatment period, the participants will be examined during a visit regarding endogenous insulin production, glycaemic control, glucose metrics and insulin doses.

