## Methods and analysis

### Study design and setting

The present study will be an investigator-initiated, multicentre, double-blind, placebo-controlled, randomised trial including 127 newly diagnosed individuals with type 1 diabetes from 17 study sites in Sweden (online supplemental material). After a run-in period of 2 weeks where blinded CGM is worn to collect baseline variables, study participants will be followed for 12 months after randomisation. Additionally, 1 and 3 years after the end of the treatment period, the participants will be examined during a visit regarding insulin production, glycaemic control, glucose metrics and insulin doses (figure 1). The trial is investigator-initiated and sponsored by the University of Gothenburg, Gothenburg, Sweden. The trial started including study participants in September 2022. The last patient is anticipated to be randomised in May 2025.

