Subjects eligible for inclusion in the study have to fulfil all of the following criteria: Signed informed consent and expected cooperation of the patients for the treatment and follow-up must be obtained and documented according to ICH GCP, and national/local regulations before trial activities are begun. Must be willing and capable of taking the study drugs and meet for tests and follow-up as described. Diagnosed type 1 diabetes (E10.9) within 100 days. First injection of insulin maximum 100 days prior to screening. If aged 36–45 years, a current insulin regimen of both basal and prandial insulin or alternatively use of an insulin pump should exist. Aged 18–45 years old. Presence of antibodies at clinical practice or at screening to at least one of the following antigens: insulin/IAA, GAD-65, IA-2 and ZnT8. Remaining stimulated peak C–peptide ≥0.20 nmol/L. If age 36–45 years, peak C-peptide should be <2.0 nmol/L. Effective contraceptive methods throughout the study.	Subjects fulfilling any of the following criteria are not eligible for inclusion in this study: Contraindications to ixekizumab. Treatment with any oral or injected glucose-lowering agents other than insulin. A history of haemolytic anaemia or significantly abnormal haematology/coagulation results at screening. Participation in other clinical trials with a new chemical entity within the previous 3 months. Subjects with severe obesity (BMI >35 kg/m^2^ if age 18–35 years and BMI >30 kg/m^2^ if age 36–45 years). Subjects with other autoimmune diseases, for example, Mb Crohn, Ulcerative colitis, Graves' disease, psoriasis, psoriatic arthritis and axial spondylarthritis, except coeliac disease and hypothyroidism, which do not need to be excluded. Active serious or chronic infections (ie, in case the patient had a serious infection (eg, pneumonia, cellulitis), has been hospitalised, has received intravenous antibiotics for an infection within 12 weeks prior to screening visit, had a serious bone or joint infection within 24 weeks before screening visit, has ever had an infection of an artificial joint. Known immunodeficiency or patient is immunocompromised to an extent that participation in the study would pose an unacceptable risk to the patient. Active or latent tuberculosis. HIV or active hepatitis B or C. Active or recurrent fungal infection. Subjects with myocardial infarction, stroke, unstable angina or heart failure in the last 6 months. Current clinically significant cardiac arrhythmias as verified by ECG. Planned surgery during the treatment period of the study (except minor surgery on skin lesions, eg, nevus). For female subjects: Positive pregnancy test, presently breast-feeding or unwillingness to use effective contraceptive measures for the duration of the study and 3 months after discontinuation. For male subjects: intent to procreate during the duration of the study or within 3 months after discontinuation or unwillingness of their partner to use effective contraceptive measures for the duration of the study and 4 months after discontinuation. Any history of malignancy in the last 5 years except for completely resected squamous or basal cell carcinoma of the skin. Administration of live attenuated vaccine(s) (LAV) within 2 months of enrolment. Or intended use of LAV during the treatment period. The investigator judges that the clinical diagnosis of type 1 diabetes set is incorrect or uncertain (needs to be confirmed by discussion with experienced diabetologist if excluding due to this criterion) Allergy against ingredients of the investigational products. Known allergy or hypersensitivity to any biologic therapy (active substance or excipients) that would pose an unacceptable risk to the patient if participating in the study. Presence of serious disease or condition, which in the opinion of the investigator makes the patient non-eligible for the study. Liver injury criteria: patients with active hepatobiliary diseases or at screening having alanine aminotransferase (ALT) or aspartate aminotransferase (AST) >2.5 times the upper limit of normal (>2.5 x ULN). Laboratory abnormalities at screening: Neutrophil count <1500 cells/μL (=1,5 *10^9^ cells/ L) Platelet count <100 000 cells/μL (= 100 *10^9^ cells/ L) Haemoglobin <8.5 g/dL (= <85 g/L) (males) and <8 g/dL (= <80 g/L) (women)

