### Study visits

The visit schedule will be as follows: randomisation, week 2, 4, 13, 26, 39 and 52. MMTT will be performed at randomisation, week 4, 26 and 52. At all visits, physical examinations will be performed and HbA1c collected. Blood pressure and weight will be taken at all visits except week 2. A detailed description of the trial procedures is provided in table 2. Additionally, participants will complete a series of questionnaires evaluating intervention treatment satisfaction, well-being, hypoglycaemia confidence, diabetes-related distress and physical activity at the study site:

Diabetes Treatment Satisfaction Questionnaire (DTSQ) is an 8-item scale measuring aspects of satisfaction scored on a 7-point Likert scale, including domains of current treatment satisfaction, convenience of treatment, understanding of diabetes, recommendation of treatment and continuation of treatment. Two versions will be used: the DTSQs and DTSQc. DTSQs is used to record current treatment satisfaction throughout the trial and the DTSQc is used to retrospectively compare the treatment arms at week 52.^16^

**Table 2 T2:** Trial procedures

	Patient info (two visits)	Screening visit (fasting*)	Baseline randomisation (fasting)	Week 2 Follow-up±1 week	Week 4 Follow-up±10 days (fasting)	Week 13 Follow-up±2 weeks	Week 26 Follow-up±2 weeks (fasting)	Week 39 Follow-up±2 weeks	Week 52 Follow-up±2 weeks (fasting)		Weeks 104 and 208 Extension phase (±3 months) (fasting)	
Variables	Visit 1	Visit 2	Visit 3	Visit 4	Visit 5	Visit 6	Visit 7	Visit 8	Visit 9		Visit 10+11	
Information visit	X											
Obtain informed consent	X											
Inclusion/exclusion criteria		X										
ECG		X										
Demographics		X										
Length		X										
Medical history		X	X						X			
Date of diagnosis of type 1 diabetes and first insulin injection		X										
Smoking status			X									
Family history of type 1 diabetes		X										
Concomitant medication		X	X	X	X	X	X	X	X			
Physical examination		X	X	X	X	X	X	X	X			
Blood pressure			X		X	X	X	X	X			
Weight		X	X		X	X	X	X	X			
Information regarding type of glucose monitoring			X			X	X	X	X		X	
GAD, ZnT8, insulin/IAA and IA-2-antibodies		X							X			
Mixed Meal Tolerance Test		X	X		X		X		X		X	
HbA1c		X	X		X	X	X	X	X		X	
Proinsulin			X						X			
Hematology†		X	X		X		X		X			
Clinical Chemistry‡		X	X		X		X		X			
Urine pregnancy test		X										
HIV, hepatitis serology, IgA transglutaminase, thyroid status		X										

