### Statistical analysis

The full analysis set (FAS-population) consists of all participants who receive at least one dose of study medication and have at least one follow-up measurement.

The per-protocol population (PP-population) consists of all participants in the full analyses set without any significant protocol deviations. The PP-population is defined at the clean file meeting before the database is locked.

The safety population consists of all participants who received at least one dose of study medication.

The primary efficacy variable, difference in change from baseline to week 52 in residual insulin secretion measured by stimulated C-peptide 2 hour area under the curve profile measured by MMTT, will be estimated by ANCOVA adjusting for differences between treatment groups in stimulated C-peptide 2 hour area under the curve at baseline. The secondary efficacy variables (difference in change in insulin need, time in glucose range, time in hypoglycaemia and HbA1c) will also be estimated by ANCOVA adjusting for difference in the evaluated variable at baseline. No interim analyses are planned in the study.

Regarding continuous exploratory variables, the difference between the two groups for normally distributed variables will be analysed using ANCOVA adjusting for baseline value and for not normally distributed variables using Fisher’s non-parametric permutation test. Dichotomous variables will be analysed using Fisher’s exact test and ordered categorical variables using Mantel-Haenszel Chi-square trend test. Statistiska Konsultgruppen, Gothenburg, Sweden, has been consulted for statistical methods.

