Several earlier studies have been performed with the aim of preserving beta cell function. These studies have targeted different immunological processes with various effects on the change in residual insulin secretion.^2334^,^37^ A difference with the current study medication, the anti-IL-17 (ixekizumab), is that it efficiently affects IL-17.

If the IL-17 signalling pathway is effectively blocked, it is possible that the destruction of beta cells in the pancreas could be halted. Preservation of beta cell function would reduce the dependency of external insulin therapy and minimise the risk of hypoglycaemia, diabetic ketoacidosis and long-term complications. The glycaemic control would likely improve, as well as quality of life. Preservation of endogenous insulin production is viewed as one of the focus areas in the development of new treatment options for people with type 1 diabetes.^38^

Strengths of the study are the randomised, double-blind, placebo-controlled study design. Another strength is the secondary outcomes that will offer information regarding insulin doses and glucose metrics measured by masked continuous glucose monitoring. Additionally, the extension phase will give further knowledge whether a potential beneficial effect is sustained over time. Limitations include the lack of data on how children respond to the treatment, and the follow-up period is relatively short at 52 weeks during ixekizumab/placebo treatment.

In summary, IL-17 is a novel pathway that has not been previously evaluated in a pivotal trial for treatment in newly diagnosed individuals with type 1 diabetes. If it preserves endogenous insulin production, it could be essential for improving glucose control, simplifying treatment regimens and reducing risk of complications in persons with type 1 diabetes. Further, it may be essential also for delaying and preventing the onset of type 1 diabetes.

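### The secondary-endpoint ANCOVAs name only each variable's own baseline; adding baseline C-peptide AUC, which is already collected, is an optional efficiency gain of unknown size

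*Protocol article*

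**What the plan says.** The Abstract of the protocol article, under Methods and analysis, introduces the clinical endpoints with "Secondary endpoints will be change in time in glucose range" and then lists the other three; it names no model. The Statistical analysis section of the protocol article gives one model for the secondary variables, described as "difference in change in insulin need, time in glucose range, time in hypoglycaemia and HbA1c". They "will also be estimated by ANCOVA adjusting for difference in the evaluated variable at baseline". The primary endpoint is analysed by "ANCOVA adjusting for differences between treatment groups in stimulated C-peptide 2 hour area under the curve at baseline". As written, baseline C-peptide AUC is a covariate for the primary endpoint and is not mentioned for the other four.

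The value is available. Under Study visits, "MMTT will be performed at randomisation, week 4, 26 and 52", and Table 2 marks the test at the randomisation visit as well as at screening. Table 2 also has insulin doses recorded at randomisation. The CGM baseline comes from the run-in: "After a run-in period of 2 weeks where blinded CGM is worn to collect baseline variables", and the Table 2 footnote has the masked sensor started at the screening visit.

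The Discussion gives the clinical rationale: "Preservation of beta cell function would reduce the dependency of external insulin therapy and minimise the risk of hypoglycaemia". It goes on to expect better glycaemic control.

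**The concern.** The sample size rests on C-peptide alone, and the article states no power for any secondary endpoint. Those endpoints are the ones that show whether preserved C-peptide matters to the patient, so their precision deserves care. If starting beta-cell reserve predicts week-52 dose and glucose beyond what the outcome's own baseline predicts, a model without it leaves explainable variance in the error term and gives a wider confidence interval than necessary.

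There is reason to think the own baseline may not carry all the information. Entry is soon after diagnosis ("First injection of insulin maximum 100 days prior to screening"), and randomisation follows within 8 weeks of eligibility. Insulin dose can therefore be recorded up to about 100 + 56 = 156 days after first insulin. The CGM baseline starts at screening and runs 14 days, so it ends by about day 100 + 14 = 114. Baseline reserve can also vary widely: the peak C-peptide criterion has a floor of 0.20 nmol/L, and a ceiling of 2.0 nmol/L only for ages 36–45.

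**Working it through.** **1. The plan's own figure.** The Sample size calculation section uses SD 0.34 nmol/L, difference 0.18 nmol/L, two-sided 0.05 and power above 80%. The allocation ratio is not stated, so 1:1 is assumed. The two-sample t-test needs 56.98 per arm, hence 57 per arm and 114 in total, with power 0.800. Dropout of 10% gives 114 / 0.90 = 126.7, rounded up to 127. Both stated figures reproduce. They concern the primary endpoint and are not affected by this point.

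**2. Formula for the gain.** Let r be the partial correlation of baseline C-peptide AUC with the week-52 secondary outcome, given that outcome's own baseline and treatment arm. Because the own baseline is in the model, r is the same whether the response is the change or the week-52 value. Adding the covariate:

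- multiplies the residual variance by (1 − r²);
- multiplies the standard error by √(1 − r²);
- is equivalent to 114/(1 − r²) − 114 extra participants;
- raises power, for an effect that had 80%, to Φ((1.960 + 0.842)/√(1 − r²) − 1.960).

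The article gives no r and no SD or effect size for any secondary endpoint. The values of r below are assumptions that span a range.

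| r (assumed) | 1 − r² | SE smaller by | Extra participants on 114 | Power, from 80% |
|---|---|---|---|---|
| 0.1 | 0.99 | 0.5% | 1.2 | 80.4% |
| 0.2 | 0.96 | 2.0% | 4.8 | 81.6% |
| 0.3 | 0.91 | 4.6% | 11.3 | 83.6% |
| 0.4 | 0.84 | 8.3% | 21.7 | 86.4% |
| 0.5 | 0.75 | 13.4% | 38.0 | 89.9% |

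Example at r = 0.3: 114/0.91 = 125.3, which is 11.3 more than 114.

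**3. Cost of the extra covariate.** At N = 114, one more covariate inflates the variance by about 109/108 = 1.0093. Net variance factors are then 1.0093 (r = 0), 0.9992 (0.1), 0.9689 (0.2), 0.9184 (0.3) and 0.8478 (0.4). Break-even is where (1 − r²) × 109/108 = 1, so r = √(1 − 108/109) = 0.096, or about 0.10. With r = 0 the standard error grows by √1.0093 − 1, about 0.5%.

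**4. Simulation check.** With N = 114, assumed correlations with the outcome were 0.3 for the own baseline and −0.4 for C-peptide, with −0.3 between the two covariates. The partial correlation is (−0.4 + 0.09)/0.91 = −0.34. The standard error fell 5.6% and power went from 0.80 to 0.85. Rejection under the null was 0.047 and 0.053 for the two models, so both hold their level. These inputs are assumptions too. They make C-peptide a better predictor than the own baseline, so the run confirms the formula and the error rate but not the likely size of the gain.

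**The case against.** The strongest reply is that nothing here is wrong. ANCOVA with the own baseline is standard, unbiased under randomisation and correct in type I error, and a second covariate is a preference. That stands, and it is why this is an efficiency point only. It is also true that the article names one covariate without saying it is the only one, and that an analysis plan not shown may name more. If it does, a confirming sentence settles the matter.

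A reader might infer three stronger things that the article does not support:

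- **That precision is definitely lost.** This needs a partial correlation above about 0.10, and none is reported. The Discussion passage concerns function preserved over time. It makes baseline C-peptide a plausible predictor, but it does not show that the baseline level predicts week 52 beyond the own baseline.
- **That the own baselines are poor because they are taken early.** This is a clinical inference. Baseline C-peptide is measured at the same visit as insulin dose, and the cohort cited for the sample size saw stimulated C-peptide fall from 0.70 to 0.46 nmol/L, so the argument cuts both ways. The 156-day limit applies to insulin dose; the CGM baseline ends by about day 114.
- **That chance imbalance in C-peptide biases the secondary results.** The confidence interval already allows for chance imbalance, and own-baseline adjustment removes the part correlated with it.

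The objection does not remove the case for the change. The covariate is already collected, naming it in advance cannot bias the result, and the loss if it proves uninformative is about half a per cent in standard error.

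**Conclusion.** The point holds as an optional, nearly free improvement and not as an error, contradiction or source of bias. It applies equally to all four secondary endpoints. HbA1c has the same model, and nothing in the article justifies leaving it out.

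The benefit is conditional. There is none at a partial correlation of about 0.10 or below, a small one at 0.2 to 0.3 (standard error 2% to 5% smaller) and a more useful one at 0.4 (about 8%). These figures assume 114 evaluable participants, 1:1 allocation and a linear covariate effect. Apart from r = 0.1 they change little when the covariate's own cost is counted.

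**What to change.** Before unblinding, state in the analysis plan that the week-52 ANCOVAs for insulin need (U/kg), time in range, time in hypoglycaemia and HbA1c each adjust for the baseline value of the evaluated variable and for baseline MMTT C-peptide AUC, defined as in the primary model. If the plan already says so, no change is needed.

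The cost is one sentence and one degree of freedom per model. No new visit, sample or assay is required. A participant without a usable baseline MMTT would need the same handling in these models as in the primary one. The timing matters: a covariate added after the results are known could be said to have been chosen because of them.

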**Ethics and dissemination:**

Approvals were obtained from the Swedish Ethical Review Authority (Dnr 2020–05098) and the Swedish Medical Products Agency (Dnr 5.1-2021-105808) before participant enrolment. Participants provide informed consent before inclusion. Results of this study will be submitted for publication in international peer-reviewed journals and key findings will be presented at international scientific conferences.

**Trial registration number:**

ClinicalTrials.gov, NCT04589325.

STRENGTHS AND LIMITATIONS OF THIS STUDYThis is a randomised, double-blind, placebo-controlled trial that examines the effect of interleukin-17 inhibition on endogenous insulin secretion in people with newly diagnosed type 1 diabetes.Secondary outcomes of the study will offer information regarding insulin doses and glucose metrics measured by masked continuous glucose monitoring.The extension phase will give further knowledge whether a potential beneficial effect is sustained over time.A limitation is that there will be no data on how children respond to the treatment.Another limitation is the relatively short follow-up period.

## Introduction

Type 1 diabetes is characterised by a destruction of insulin-producing beta cells in the pancreas.^1^ The development of type 1 diabetes occurs in three stages: In stage 1, asymptomatic individuals have the presence of >2 pancreatic autoantibodies; in stage 2, impaired glucose tolerance is seen; and in stage 3, type 1 diabetes eventually develops.^2^ Thereafter, in most individuals, there is a gradual loss of the remaining insulin-producing cells after diagnosis over a period of several years, or even decades.^3^,^5^ These long-lasting beta cells remain functional decades after diagnosis, as evidenced by increased secretion of C-peptide in response to a mixed meal.^6^

Already in the beginning of the year 2000, several studies suggested that interleukin (IL)-17 plays a key role in the destruction of beta cells and the development of type 1 diabetes.^7^,^15^ In the Ixekizumab Diabetes Intervention Trial (I-DIT), we aim to evaluate if endogenous insulin secretion can be preserved or increased in people with newly diagnosed type 1 diabetes by inhibition of IL-17 compared with placebo in addition to their conventional therapy. We will also evaluate change in glucose metrics measured by masked continuous glucose monitoring (CGM), HbA1c, mean insulin doses per kilogram body weight and various patient-reported outcomes.

